#### **2.3.9.2. Statistical analyses**

Statistical analyses will be done by the postdoctorate under the supervision of [name]. We will present descriptive statistics for the proportions of women first authors that were: rejected without external review; sent for external peer review; rejected, accepted or invited to revise a manuscript after external peer review; and rejected and accepted after revision. To take into account clustering at the journal level, we will perform mixed-effects logistic regression to model the influence of the first author's gender on the odds of acceptance for publication, after adjustment for the confounders and covariates (cf. appendix 7) and using the journal as a random effect. We will perform the same logistic regression model to answer our secondary objectives to study the influence of corresponding-author gender or last-author gender on the acceptance for publication. To test whether the handling editor's gender or reviewers' gender modifies the association between first-author gender and the acceptance rate, we will include an interaction term between these two predictors. We will also test interactions of first author gender, respectively with the scope of the journal and with time on a yearly scale. Journals will be anonymised, therefore separate journal effects will not be presented when we publish the results but we will provide journal level data to individual journals upon request.

In the retrospective cohort, we will describe and compare, using Chi-2 tests, the proportion of women first authors for articles at the following points in the decision-making process: rejection without review; sent for peer review; rejected, accepted and sent for revision after peer review; and between articles rejected at any stage versus articles accepted for publication. To test whether the reasons for rejection mentioned in decision letters varies between men and women first (then corresponding and last) authors, we will include an interaction term between these two predictors in a mixed-effects logistic regression model with rejection as the dependent variable and journal as the random factor. All analyses will be performed using STATA 17.0 IC (StataCorp LP, College Station, TX, USA) and R software (version 4.0.5).

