#### 2.3.7.2. Exposure variables and other confounders

The main exposure factor of interest is **first-author gender**. Other exposure factors assessed are: corresponding and last-author gender, handling-editor gender.

We will also collect data on: year of submission, study design, sample size, statistical significance of main results, funding disclosure, first author’s country of affiliation (reflecting somehow the author’s ethnicity/race), number of authors on the byline, number of reviewers who peer reviewed the manuscript, number (proportion) of women among all reviewers, number (proportion) of reviewers with same region of affiliation as the first author, and first author’s degrees (MD, PhD). If available, we will extract the reasons for rejection mentioned in the journal decision letter.

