## THE ATHENA STUDY: FIRST AUTHOR'S GENDER AND ACCEPTANCE FOR PUBLICATION

**Appendix 7.** Data extracted for the case-control study.

| Variables                                                  | Description                                                                                                                                                                                                                                          |
|------------------------------------------------------------|------------------------------------------------------------------------------------------------------------------------------------------------------------------------------------------------------------------------------------------------------|
| Unique ID of manuscript                                    | tracking number generated during submission process                                                                                                                                                                                                  |
| Journal identifier                                         | ##                                                                                                                                                                                                                                                   |
| Scope of the journal                                       | 1= infectious diseases journal 2= family medicine 3=internal medicine
4=others                                                                                                                                                                    |
| Date of submission                                         | __ / __ / ____                                                                                                                                                                                                                                       |
| Handling editor's gender                                   | 0=man, 1=woman                                                                                                                                                                                                                                       |

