| Number of authors on the byline                            | ##                                                                                                                                                                                                                                                   |
| Degrees for the first author                               | 1=MD, 2=PhD, 3=MSc or equivalent, 4=RN, 5=mixed PhD & MD...                                                                                                                                                                                          |
| First author's gender                                      | 0=man, 1=woman                                                                                                                                                                                                                                       |
| Corresponding author's gender                              | 0=man, 1=woman                                                                                                                                                                                                                                       |
| Last author's gender                                       | 0=man, 1=woman                                                                                                                                                                                                                                       |
| Funding source                                             | 1=private, 2= public, 3=NGO, 4=mixed                                                                                                                                                                                                                 |
| Reviewers' degrees                                         | 1=MD, 2=PhD, 3=MSc or equivalent, 4=RN, 5=mixed PhD & MD...                                                                                                                                                                                          |
| Number of submissions                                      | #                                                                                                                                                                                                                                                    |

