| Number of revisions                                        | #                                                                                                                                                                                                                                                    |
| Number of reviewers                                        | #                                                                                                                                                                                                                                                    |
| Number (proportion) of women reviewers                     | #                                                                                                                                                                                                                                                    |
| Number of reviewers from same region as
first author    | #                                                                                                                                                                                                                                                    |

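### The primary model's covariates are fixed only by pointing to Appendix 7, which includes number of revisions and reviewer variables; entering number of revisions would change what the gender odds ratio estimates

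*Protocol*

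**What the plan says.** Section 2.3.9.2 specifies a mixed-effects logistic regression of acceptance on first-author gender, "after adjustment for the confounders and covariates (cf. appendix 7) and using the journal as a random effect". That pointer is the section's only definition of the adjustment set.

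Appendix 7 is titled "Data extracted for the case-control study". Nothing in it marks which variables enter a model. Besides manuscript attributes it holds "Number of revisions", number of reviewers, "Number (proportion) of women reviewers", reviewers from the first author's region, and reviewers' degrees. It also holds the manuscript identifier, the exposure itself ("First author's gender") and "Corresponding author's gender".

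Section 2.3.7.2, whose heading covers exposures and confounders, gives a different list. It includes "number of authors on the byline, number of reviewers who peer reviewed the manuscript, number (proportion) of women among all reviewers", but neither number of revisions nor reviewers' degrees. It names the first author's country of affiliation, whereas Appendix 7 has only the study country.

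Three other places matter. Section 2.5.1 describes a request for revision as one of the editor's possible initial decisions. Section 1.2 makes bias at the first and last editorial decisions a study aim. Section 2.3.9.2 describes the share of women among papers invited to revise, as a result in its own right.

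**The concern.** The primary question is whether first-author gender affects acceptance after peer review. By section 2.5.1, being asked to revise is a step between submission and acceptance, and it is decided by the editors whose behaviour is under study. A covariate on that path is not a confounder. Conditioning on it takes out any gender effect that runs through the invitation to revise and leaves a different quantity: roughly, the gender difference among papers with the same revision history. Number of revisions is also likely to predict case status strongly, which costs precision.

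Reviewer number, gender, region and degrees are weaker cases of the same problem. They are settled after submission, so they may mediate an effect of author gender, but they precede the editor's decision and are not produced by it.

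Interpretation is at stake. Section 1.4 plans to read an absence of bias in editors' and reviewers' decisions as evidence that discrimination lies further upstream. An odds ratio drawn towards 1 by its own adjustment would give that reading false support.

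**Working it through.** **Inputs from the protocol.** Target OR 0.85; women first authors 40% of cases and 44% of controls; 2800 per group (section 2.3.9.1). The stated OR reproduces: (0.40/0.60)/(0.44/0.56) = 0.848. The protocol gives no revision or acceptance rates and no figure for this issue, so the rest rests on assumed inputs.

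**Assumed process.** An editor invites revision or rejects. A small share of the favoured papers is accepted without revision; the others are revised and then accepted or rejected. Cases and controls are sampled 1:1, which leaves the odds ratio unchanged. The journal random effect is omitted.

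**Bias at the first decision only.** Take 50% of men's papers favoured, OR 0.82 for women at this step, 3% of favoured papers accepted unrevised, and 85% of revised papers accepted for both sexes.
- Men: P(accept) = 0.50 × (0.03 + 0.97 × 0.85) = 0.427; odds 0.746.
- Women: P(favoured) = 0.82/1.82 = 0.451; P(accept) = 0.451 × 0.8545 = 0.385; odds 0.626.
- Total OR = 0.626/0.746 = 0.84.
- Among revised papers, acceptance is 85% for both sexes, so OR = 1. Among unrevised papers, OR = 0.82, but few accepted papers are there. The adjusted OR is a blend weighted towards 1.

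**Bias after revision only.** Take 50% favoured for both sexes, 70% of men's revised papers accepted, and OR 0.73 for women at this step.
- Women: acceptance odds after revision = (0.70/0.30) × 0.73 = 1.703, so 63.0%.
- P(accept): men 0.50 × (0.03 + 0.97 × 0.70) = 0.3545; women 0.50 × (0.03 + 0.97 × 0.630) = 0.3206.
- Total OR = (0.3206/0.6794)/(0.3545/0.6455) = 0.86.
- Among revised papers OR = 0.73, so adjustment moves the estimate away from 1.

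**Simulated logistic fits:**

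| Where bias acts | Accepted after revision (men) | Accepted unrevised, of favoured | OR, unadjusted | OR, count of revisions added | OR, any/none added |
|---|---|---|---|---|---|
| First decision | 85% | 3% | 0.84 | 0.92 | 0.95 |
| First decision | 70% | 3% | 0.85 | 0.92 | 0.97 |
| First decision | 85% | 10% | 0.84 | 0.90 | 0.91 |
| Both stages (OR 0.87 each) | 85% | 3% | 0.85 | 0.87 | 0.87 |
| After revision | 70% | 3% | 0.86 | 0.81 | 0.77 |

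Other input sets with bias at the first decision (35–60% invited, 80–90% accepted after revision, 1–5% of accepted papers unrevised) gave 0.93–0.97 with the count and 0.94–0.99 with any/none. Other sets with bias only after revision went as low as about 0.66. Across sets the standard error of the gender coefficient rose about 1.3- to 2.6-fold.

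**What that does to precision.** With 1120 and 1680 women and men among cases and 1232 and 1568 among controls, the unadjusted SE of the log OR is √(1/1120 + 1/1680 + 1/1232 + 1/1568) = 0.054.
- OR 0.85, unadjusted: 95% interval 0.76–0.94.
- OR 0.92, SE × 1.3: 0.80–1.06.
- OR 0.97, SE × 2.6: 0.74–1.28.

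**The case against.** The strongest reply is that the protocol nowhere says every Appendix 7 variable is entered. The appendix holds the manuscript identifier and the exposure, so it cannot be the literal covariate set, and section 2.3.7.2 leaves out number of revisions. A final covariate list is also commonly left to the SAP. The first part stands: a reader might infer that the primary model will adjust for number of revisions, and the document does not establish that. The second part does not dispose of the point. The protocol does fix a source for the adjustment set; that source contains a step of the outcome process, nothing excludes it, and the other list puts reviewer variables under a confounder heading.

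A reader might also infer that adjustment removes the gender effect. No general claim of that kind holds: the table shows attenuation, almost no change, or exaggeration, depending on the stage at which bias acts.

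A reader might further infer from Appendix 7 that corresponding-author gender enters the primary model and splits the exposure effect. Section 2.3.7.2 classes corresponding- and last-author gender as other exposures, and section 2.3.9.2 gives them analyses under the secondary objectives, so separate models are the natural reading.

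Finally, the unadjusted stage-by-stage description in section 2.3.9.2 could reveal a gender difference at the invitation to revise. That limits the risk of misreading but does not repair the primary estimate.

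**Conclusion.** The concern holds in a limited form. The adjustment set is fixed badly: the only pointer leads to an extraction list that mixes attributes fixed at submission with an editorial decision on the path to acceptance and with possible mediators, and it disagrees with section 2.3.7.2. If number of revisions is entered, the OR stops estimating the total effect. A total OR of about 0.86 becomes about 0.92–0.97 with bias at the first decision (extremes 0.90 and 0.99 across the sets tried), changes little with bias split over both stages, and becomes about 0.66–0.81 with bias only after revision. The standard error grows roughly 1.3- to 2.6-fold.

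These sizes rest on assumed invitation and acceptance rates and on models without the journal effect. That conditioning on a step of the outcome process changes the estimand does not depend on them. No size is claimed for the reviewer variables, which were not modelled.

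**What to change.** In section 2.3.9.2, replace the pointer to Appendix 7 with a named list of primary covariates limited to manuscript and author attributes fixed at submission: year of submission, study design, sample size, significance of the main result, funding, multicentre status, number of authors, and the first author's degree and country of affiliation. Then state that:
- number of revisions is not a covariate;
- reviewer number, gender, region and degrees are used only in the planned interaction or in mediation or sensitivity analyses;
- corresponding- and last-author gender are analysed in their own secondary models.

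Align section 2.3.7.2 and mark the role of each variable in Appendix 7. The cost is a few sentences and no additional data, provided the change is made before the analysis.

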### 2.3.3. Objectives

Our **primary objective** is to evaluate the influence of first-author gender on acceptance rates of original articles submitted to leading medical journals that were sent for peer review.

Our **secondary objectives** are: 1) to study the influence of corresponding-author gender and last-author gender on acceptance for publication; 2) to test whether the editor's or associate editor's (see glossary) gender modifies the influence of author gender on acceptance for publication; 3) to determine whether the influence of author gender on acceptance for publication varies over an eight-year period; 4) to determine the proportion of women first authors at each stage of the editorial decision-making process; 5) to possibly explore whether the reasons for manuscript rejection differ between women and men first, last and corresponding authors.

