#### 2.3.8.1. Data extraction

##### 2.3.8.1.1. Extraction for the case-control study

We will complete data extraction (study design, statistical significance of main result, etc.) from the manuscripts by using text mining techniques. For this specific task, we will collaborate with the Swiss Institute of Bioinformatics (SIB), Bibliomics and Text Mining Group (BiTeM, [name]) through a study partnership. All prespecified variables will be automatically extracted using an algorithm created by our project partner at the SIB and recorded in a database. Data on manuscripts, authors, editors and reviewers involved will be obtained directly from the journals and merged with the dataset (list of variables; see appendix 7).

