#### **2.3.8.1.4. Final dataset for case-control study**

We will disaggregate the editorial decision variables from the submission data so that determination of author's gender and all other data extraction will be done blinded to editorial decision. Finally, for analysis we will combine the separate databases using the manuscript identity number.

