#### **2.3.10. Ethical considerations**

As the project will not involve human participants but data routinely collected from articles submitted for publication in various medical journals, we do not expect any major ethical issues. However, to guarantee the anonymity of the authors, reviewers, and editors, we will remove personal identifying variables from the final database, all names of individuals will be removed and only their gender included. We will also preserve journal anonymity by presenting results without naming the journals; journals will be identified by a coded variable. The protocol was submitted to the Geneva Cantonal Ethics Commission on March 23, 2019. It was exempted from ethical approval on April 24, 2019 but received full support (appendix 1). Personal data will be provided by journals under confidentiality agreements or research contracts.

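### The editor-gender interaction has no editor level and the described dataset lists no editor code, so its standard error may be too small if the author-gender effect differs between editors

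*Protocol*

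**What the plan says.** - **Objective.** Protocol section 2.3.3, secondary objective 2, asks whether the editor's or associate editor's "gender modifies the influence of author gender on acceptance for publication". Section 1.3 also names the handling editor's gender as an effect modifier.
- **Model.** Section 2.3.9.2 states: "To take into account clustering at the journal level, we will perform mixed-effects logistic regression", "using the journal as a random effect". For effect modification, the same section tests whether the handling editor's (or reviewers') "gender modifies the association between first-author gender and the acceptance rate, we will include an interaction term between these two predictors". No editor-level random effect, random slope or cluster-robust variance is named.
- **Data kept.** Section 2.3.10 says of individuals that "all names of individuals will be removed and only their gender included", whereas "journals will be identified by a coded variable". The case-control variable list in Appendix 7 has a row for the handling editor's gender, coded 0 or 1, and none for an editor identifier.
- **Data flow.** Section 2.3.8.1.1: "Data on manuscripts, authors, editors and reviewers involved will be obtained directly from the journals and merged with the dataset". Section 2.3.8.1.4: "for analysis we will combine the separate databases using the manuscript identity number".

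**The concern.** Editor gender belongs to the editor, not to the manuscript. Up to 320 sampled manuscripts per journal (160 cases and 160 controls, section 2.3.9.1) are shared among that journal's editors, and section 2.5.1 says the final decision may rest with a single handling editor.

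If individual editors of the same gender differ in how author gender affects their decisions, the comparison of women with men editors carries a variance component that shrinks with the number of editors, not with the number of manuscripts. A model clustered on journal alone leaves that component out. A few atypical editors could then be reported as an effect of editor gender.

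The dataset description adds to the problem: an analyst working from the file as described would have no variable with which to add the editor level or check for it.

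**Working it through.** **Plan's own figure.** The Protocol gives no precision, power or error figure for the interaction, so there is none to reproduce. Its sample size is for the primary comparison and allows for clustering by journal only.

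**Inputs from the Protocol.** 23 journals; 1:1 cases and controls within journal; women first authors 40% of cases and 44% of controls, so about p = 0.42 overall; two-sided 5% test.

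**Assumptions, because the Protocol is silent.** 3, 10 or 20 handling editors per journal; 35% women editors; between-editor SD of acceptance (log odds) 0 to 0.5; between-editor SD τ of the author-gender log odds ratio 0 to 0.3.

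**Step 1: analytic check.** For an editor with m manuscripts, half of them cases, the sampling variance of that editor's author-gender log odds ratio is about 1/(m × 0.42 × 0.58 × 0.25) = 1/(0.0609 m). Variation between editors adds τ². The true standard error of the interaction divided by the model's is therefore √(1 + 0.0609 m τ²), and the true level of the nominal 5% test is 2 × [1 − Φ(1.96/ratio)]. With 300 manuscripts per journal, m is 100, 30 or 15.

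Worked case, m = 100 and τ = 0.3: 0.0609 × 100 × 0.09 = 0.548; √1.548 = 1.244; 1.96/1.244 = 1.575; level 11.5%.

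**Step 2: simulation.** 23 journals × (150 cases + 150 controls), true interaction zero, 1500 runs per setting, logistic regression without an editor term. The journal intercept was left out because 1:1 sampling within journal makes it about zero. The SD of acceptance between editors was 0.3 for τ = 0.1 and 0.2, and 0.5 for τ = 0.3.

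| Editors per journal (m) | τ | SE ratio, analytic | Level, analytic | Level, simulated | Level with editor-clustered SE |
|---|---|---|---|---|---|
| 3 (100) | 0.1 | 1.030 | 5.7% | 5.9% | 6.4% |
| 3 (100) | 0.2 | 1.115 | 7.9% | 7.6% | 5.3% |
| 3 (100) | 0.3 | 1.244 | 11.5% | 11.9% | 7.4% |
| 10 (30) | 0.1 | 1.009 | 5.2% | 5.1% | 4.7% |
| 10 (30) | 0.2 | 1.036 | 5.9% | 5.8% | 5.3% |
| 10 (30) | 0.3 | 1.079 | 6.9% | 6.1% | 4.2% |
| 20 (15) | 0.1 | 1.005 | 5.1% | 4.8% | 4.6% |
| 20 (15) | 0.2 | 1.018 | 5.4% | 5.1% | 5.1% |
| 20 (15) | 0.3 | 1.040 | 6.0% | 6.7% | 5.9% |

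The Monte Carlo standard error is √(0.05 × 0.95/1500) = 0.6 percentage points. With no editor variation at all, the simulated level was 4.9%, 6.3% and 5.7% for 3, 10 and 20 editors. Differences of about a point in the table should not be read as real.

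**Step 3: editors differ only in overall acceptance** (SD 0.3 to 0.5, τ = 0). The interaction's level was 4.8% to 5.3%, and the empirical SD was 0.98 to 1.02 times the model standard error. There is no narrowing, because first-author gender varies within each editor and a shared editor intercept largely cancels from the contrast.

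**Step 4: editor-gender main effect.** Section 2.3.7.2 lists handling-editor gender as an exposure in its own right. Whenever editors varied in acceptance, the level of its test was 5.8% to 26.1%. This is the term that the missing editor level distorts most.

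**Step 5: after missing data.** With the 2800 + 2800 = 5600 manuscripts the plan needs after losses, m falls to 5600/(23 × 3) = 81 at 3 editors. At τ = 0.3 the ratio is √(1 + 0.0609 × 81 × 0.09) = 1.20 and the level about 10%, a little lower than in the table.

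**The case against.** Four arguments have weight.

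1. **The interaction already models editor gender.** Objective 2 supposes a difference between women and men editors, which the fixed term captures. The problem needs further variation among editors of the same gender, which the Protocol does not hypothesise. This stands, and it is why the conclusion is conditional. A reader might infer that the interval is too narrow in any case. Step 3 shows that it is not.

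2. **The information is not lost.** A reader might take the rule on names in section 2.3.10 to make the clustering impossible to correct. The Protocol does not support that. Journals supply the editor data, the manuscript number is the merge key, and nothing forbids a coded editor variable. The restriction to gender cannot be wholly literal either, because Appendix 7 also keeps first-author and reviewer degrees. Nor is Appendix 7 complete: the editor's geographical affiliation (section 1.3) and the reasons for rejection (section 2.3.7.2) are planned but have no row. What stands against this is that no editor code is provided for, while one is for journals.

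3. **Random slopes and robust variances belong in a statistical analysis plan.** That is fair for the choice of method. But the Protocol fixes the contents of the file, and no later plan can cluster on a variable that the file lacks.

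4. **The upper end of the range is a corner.** The study's target odds ratio of 0.85 is a log odds ratio of 0.16 in size, so τ = 0.3 is about 1.8 times that. Around an odds ratio of 1 it puts 95% of individual editors between exp(−1.96 × 0.3) = 0.56 and exp(1.96 × 0.3) = 1.80. Combining this with only 3 editors per journal over eight years is unfavourable. Where a committee decides, which section 2.5.1 allows, variation by handling editor may also be smaller. With 10 or 20 editors and τ up to 0.2, the excess is hardly visible.

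**Conclusion.** The point holds in conditional form. Journal is the only clustering level for a declared secondary objective, and the dataset as described has no editor code with which to change that. The interaction's standard error is too small if, and only if, the author-gender effect varies between editors of the same gender.

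Under the assumed 3 to 20 editors per journal and SD of 0.1 to 0.3, the true level of the nominal 5% test runs from about 5% to 12%, and from about 5% to 8% at SD 0.2. The standard error is understated by a factor of at most about 1.25, and that only with few editors handling many papers each. The editor-gender main effect is more exposed, since ordinary differences in editors' acceptance rates are enough to distort it.

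Both inputs that drive the size are assumptions. The primary analysis of first-author gender is not put in doubt by this point.

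**What to change.** - **Data.** Assign a pseudonymous handling-editor code when the journals' data are merged and before names are removed, as is already planned for journals. Add a row for it to Appendix 7, and reword section 2.3.10 so that it allows coded, non-identifying variables for editors.
- **Model.** Fit the editor-gender interaction with a random intercept and a random first-author-gender slope for editor within journal. If the slope cannot be estimated, use editor-clustered standard errors. Report the number of editors of each gender beside the result.

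**Cost.** One coded column and one extra model term. The interval for a secondary test may widen. Some small-cluster error can remain: editor-clustered standard errors gave 4.2% to 7.4% in the simulated settings with varying slopes, with 7.4% where the unadjusted level was 11.9%. With 10 or 20 editors per journal there are only about 24 or 12 analysable manuscripts per editor (5600/230 and 5600/460), so the random slope may be poorly estimated. The code must also be kept non-identifying, because combined with journal, date and gender it is not automatically anonymous.
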